### Secondary outcomes (falls, quality of life, psychiatric status, cognitive functioning)

Estimations of the primary outcome (incidence of delirium) was used for the calculation of the overall sample size of our study. For secondary analyses, it is assumed that 80% (∼1000 patients) of the trial population will have completed the 30-day and 1-year follow-up survey. With a sample size of 1000 patients, it should be possible to detect a difference of 0.5 points (SD of 2.5) in mean score of the Physical Health Score from baseline to 30-day and 1-year follow-up survey between the usual care and guided group with a power of >80% and a 2-sided alpha level of p<0.05. Secondary outcomes and exploratory analyses will be examined in a number of ways; including multivariable regressions.

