## Methods

### Overview of the research design and study subjects

The Research Ethics Boards of the Montreal Heart Institute (2017-2164), the University of Manitoba (HS18290), Kingston University (ANAE-298-16), and the University of Toronto (17-5933) all approved the study. The details of the design of the ENGAGES-Canada study are included in this protocol and it contains the complete list of elements from the SPIRIT (Standard Protocol Items: Recommendations for Interventional Trials) checklist
^
29,
30
^. This study was registered with ClinicalTrials.gov (
NCT02692300) on 26 February 2016.

 The ENGAGES-Canada will randomize 1200 patients of 60 years old and older in a clinical trial designed to be pragmatic. The first patient randomized in the trial was enrolled in November 2016. Competent patients who provide informed consent and who are undergoing elective cardiac surgery with cardiopulmonary bypass are eligible to be included in the study. There are no absolute contraindications to EEG monitoring, and the design of the ENGAGES-Canada trial is largely pragmatic. Exclusion criteria include positive preoperative delirium screening. In addition, patients with hearing impairment, and those who are blind, illiterate, or do not speak French or English will be excluded because they will not be able to participate adequately in delirium screening. Finally, patients who have previously had general anesthesia and who have reported experiencing intraoperative awareness will also be excluded
^
31
^.

Participants are randomized to either one of two groups: in the guided group, anesthetic administration is guided largely by EEG waveform; in the other group, patients receive current usual anesthetic care for cardiac surgery. Delirium and other assessments take place preoperatively, and delirium is assessed postoperatively from day one to five while the patient is in the hospital. The primary outcome will be the incidence of postoperative delirium. As secondary and other outcomes, we will also examine stress reaction and dissociation at discharge as potential factors associated with delirium and predictors of postoperative psychiatric symptoms. At 30-days and at 1-year, follow-up assessments include the quality of life as related to health, cognitive functioning, and information on psychiatric symptoms and on the incidence of falls – collected via self-report.

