### Randomization and blinding

Computer-generated assignment at the patient level is used for randomization. Patients who are eligible, and have given informed consent, are randomized to either usual care or to the protocol for guided anesthesia according to the EEG. A one to one ratio of randomization of the patients between usual care and the protocol for EEG-guidance is used. Within the research team, members are trained to enroll participants and assign the randomization between the usual care or the protocol for EEG-guidance. Anesthesiologists and their team learn of the group assignment after the patient is brought into the operating room; an opaque, sequentially numbered, sealed envelope is opened to reveal the study group. The randomization sequence is generated by the data analysis center. The anesthesiologist and the team caring for the patient intraoperatively are not blinded to the group assignment. The patients and family members are not aware of the group assignment. The research team members who are in charge of the assessment of delirium postoperatively remain blinded to the group assignment. Chart reviews are conducted by individuals blinded to the group assignment and blinded to the outcome of the postoperative delirium assessments
^
29,
30
^. Predictability of the randomization sequence is minimized by recording in a separate document, unavailable to the members of the research team who enroll participants and assign groups, the details of patients who have already been randomized.

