### Outcomes

The primary outcome is the occurrence of incident delirium on postoperative days 1-5. Secondary outcomes include: length of ICU and hospital stay; duration and severity of delirium POD 1-5; incidence of falls and association between delirium and falls at 30 days and at 1 year; association between delirium and quality of life by PROMIS Global Health; predictors of Post-Traumatic Stress Disorder (PTSD) by PDEQ at 5 days and 30 days postoperatively; and predictors of Post-Traumatic Stress Disorder (PTSD) by PDEQ at 5 days and 30 days postoperatively. Exploratory outcomes include co-variates of delirium, functionality, and cognitive impairment at 30 days and at 1 year postoperatively. Pre-specified exploratory analyses include intraoperative mediating events such as anesthetic concentrations, electroencephalogram suppression time, and hypotension duration. Perioperative adverse events include undesirable intraoperative movement, awareness with recall, complications such as major blood loss and transfusions, stroke, sternal wound infection, sepsis, dialysis, prolonged intubation, and mortality rates at 30-day and at 1-year.

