### Sample size calculation statistical analyses

Based on previous studies in cardiac surgery patients, we conservatively estimated a delirium incidence in the control group of 25%
^
2–
9
^ and based on meta-analyses of randomized trials we estimated a relative reduction in delirium with guidance of anesthesia based on EEG waveform of more than one-third
^
3,
7,
24
^. Assuming a two-sided alpha <0.05 and 1200 patients, we estimated >90% power to be able to detect an absolute decrease in the incidence of delirium of 8%
^
27
^. With a more stringent two-sided alpha <0.005, we estimated >70% power. We anticipate that most patients will be available for primary outcome ascertainment (i.e. incident postoperative delirium assessment). Continuous variables will be presented as mean (SD) or median (interquartile range [IQR]), depending on their distributions. Chi-square or Fisher’s exact tests will be used for comparisons of discrete data. Unpaired Student’s t or Mann–Whitney U tests will be used for comparisons of continuous data, depending on their distributions. Confidence intervals for median differences will be calculated using Hodges-Lehmann estimates, and for differences between proportions we will use Newcombe’s method with continuity correction
^
53
^. For the primary outcome, the proportion of patients with incident postoperative delirium will be compared between the two study groups. We will conduct three post-hoc sensitivity analyses to assess whether improved clinician fidelity to the guided protocol might alter the primary outcome. Within the guided group 25% of cases will be excluded with the (1) longest cumulative electroencephalogram suppression time; (2) longest cumulative time with BIS, WAVcns <40 or PSi <25; and (3) highest median volatile anesthetic concentrations. To compare time to delirium onset between groups, we will construct Kaplan-Meier curves for each group and conduct a log-rank test. We will perform a covariate adjustment including likely risk factors for delirium (including age, sex, history of depression, history of delirium, AD* Test, Short Blessed Test, comorbidity index, and study center) using two methods: (1) logistic regression and (2) standardized estimator combined with bootstrapped 95% confidence intervals (CIs)
^
54
^. We will compare delirium incidence between groups, segregated by Charlson Comorbidity Index categories
^
55

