^. Patients will be assessed based on their randomization group in accordance with an intention-to-treat approach. We will also conduct a per protocol sensitivity analysis: when clinicians in the usual care group view EEG data, these patients will be included in the guided group; and where there are technical difficulties in viewing electroencephalogram data in the guided group, these patients will be included in the blinded group. Patients who cannot be assessed for delirium will be excluded from the primary outcome analysis. In two sensitivity analyses, these patients (unless they die during surgery) will either all be assumed to have had incident delirium or not to have had incident delirium. We will compare preoperative characteristics between respondents and alive non-respondents to 30-day postoperative surveys. We will do the same for the 1-year postoperative surveys. Results will be presented with 95% CIs. All significance testing will be two-sided, with P values <0.05 considered as providing suggestive evidence and P values <0.005 as providing more compelling evidence
^
56
^. The statistical analyses will be performed with
SAS, V.9.4 (SAS Institute, Cary, North Carolina) and/or
STATA, V.14.2 (StataCorp LP, College Station, Texas).

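### Name one baseline-adjusted analysis for the between-arm quality-of-life comparison, say which SD the 2.5 is, write 960 for 80% of 1200, and give the outcome one definition and one rank

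*Protocol article*

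**What the plan says.** **Power and follow-up.** Under Secondary outcomes (falls, quality of life, psychiatric status, cognitive functioning), the Protocol article states that "it is assumed that 80% (∼1000 patients) of the trial population will have completed the 30-day and 1-year follow-up survey". With 1000 patients it then claims more than 80% power, at two-sided 5%, to "detect a difference of 0.5 points (SD of 2.5) in mean score of the Physical Health Score from baseline to 30-day" and to 1 year, between usual care and guided care. It does not say whether 2.5 is the SD of the change or of the score at one time.

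**Analysis.** Sample size calculation statistical analyses gives a general rule: unpaired t or Mann–Whitney "tests will be used for comparisons of continuous data, depending on their distributions". The secondary-outcomes section adds only that several approaches will be used, multivariable regression among them. On non-response the analysis text says: "We will compare preoperative characteristics between respondents and alive non-respondents to 30-day postoperative surveys", with the same at 1 year.

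**Data.** PROMIS Global Health is collected preoperatively, at 30 days and at 1 year.

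**Definition and rank of the outcome.** The Outcomes section lists as secondary the "association between delirium and quality of life by PROMIS Global Health". The Abstract lists quality of life itself as secondary. Table 1 puts postoperative quality of life among the other exploratory outcomes. Pre-specified additional analyses and sub-studies, item c, again has the association of quality of life with delirium.

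**The concern.** The quantity that is powered is a difference between arms in change from baseline, and the only tests named for continuous data make no use of a covariate. A change score uses the baseline inefficiently: unless baseline and follow-up are almost perfectly correlated, subtracting the baseline leaves more variance than regressing on it. The baseline is collected anyway, so the precision is there to be taken.

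The undefined SD also matters. If 2.5 describes the raw score, the power of an unadjusted change score depends strongly on a correlation that the protocol does not give, and the stated power may not hold.

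Two further points affect how the result is read. The stated number of completers does not match its own percentage. The quality-of-life outcome appears as a comparison of randomised arms in one place and as an association with delirium in another. These are different questions, and only the first is protected by randomisation.

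**Working it through.** **Inputs from the protocol.** 1200 randomised (Overview of the research design and study subjects); 1:1 allocation (Randomization and blinding); 80% survey completion, written as about 1000; difference 0.5; SD 2.5; two-sided alpha 0.05; power above 80%.

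**Assumptions of this check.** The correlation r between baseline and follow-up scores is not in the protocol and is varied. Score variance is taken as equal at baseline and follow-up.

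**1. The plan's own figure.** With n per arm, power ≈ Φ(0.5 / (SD × √(2/n)) − 1.960).
- 1000 patients, n = 500: standard error 2.5 × √(2/500) = 0.158; 0.5/0.158 = 3.162; Φ(1.202) = 88.5%. The stated >80% is reproduced.
- For exactly 80% power, 393 per arm (786 in all) would be enough.

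**2. The number of completers.** 0.80 × 1200 = 960, and 1000/1200 = 83.3%. At n = 480: standard error 0.161; 0.5/0.161 = 3.098; Φ(1.138) = 87.3% (87.2% with the t distribution). The power claim holds with either number.

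**3. Effect of baseline adjustment.** With score variance s², the change score has variance 2s²(1 − r) and the baseline-adjusted residual has variance s²(1 − r²). The ratio is (1 + r)/2, which is below 1 for any r < 1.

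If 2.5 is the SD of the **change**, the adjusted SD is 2.5 × √((1 + r)/2). At 960 patients:

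| assumed r | change-score power | adjusted SD | adjusted power |
|---|---|---|---|
| 0.3 | 87.3% | 2.016 | 97.0% |
| 0.5 | 87.3% | 2.165 | 94.7% |
| 0.7 | 87.3% | 2.305 | 91.9% |
| 0.8 | 87.3% | 2.372 | 90.4% |

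If 2.5 is the SD of the **raw score**, the change SD is 2.5 × √(2(1 − r)) and the adjusted SD is 2.5 × √(1 − r²). At 960 patients:

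| assumed r | change SD | change-score power | adjusted SD | adjusted power |
|---|---|---|---|---|
| 0.3 | 2.958 | 74.5% | 2.385 | 90.1% |
| 0.4 | 2.739 | 80.7% | 2.291 | 92.2% |
| 0.5 | 2.500 | 87.3% | 2.165 | 94.7% |
| 0.7 | 1.936 | 97.9% | 1.785 | 99.1% |

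Under the raw-score reading, an unadjusted change score drops below the stated 80% somewhere between r = 0.3 and r = 0.4. The adjusted analysis stays above 90% in every row of both tables.

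**4. The outcome side by side.**

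| Place | What is listed | Rank |
|---|---|---|
| Abstract | quality of life | secondary |
| Outcomes | association of delirium with PROMIS Global Health | secondary |
| Table 1 | postoperative quality of life | other exploratory |
| Secondary outcomes section | between-arm difference in Physical Health Score | powered, under a secondary heading |
| Additional analyses, item c | association of quality of life with delirium | additional analysis |

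These entries give two definitions and more than one rank.

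**The case against.** A reader might infer that the protocol fixes an unadjusted change-score comparison among responders. It does not. The sentence on 0.5 points is a power statement, the t/Mann–Whitney sentence is a general rule that does not mention quality of life, and multivariable regression is named for the secondary outcomes and could include the baseline score. This is also a condensed article, and an analysis plan that is not shown may set the model and the handling of missing scores. That objection stands, so adjustment is recommended here as an improvement in efficiency.

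A reader might also infer that patients who answer only one survey are lost. The document does not say so. Analysing each time point on those who replied then would already keep them. The overlap of responders is not given, so any gain from a longitudinal model cannot be sized, and such a model does not deal with deaths before follow-up. Nor is non-response ignored in the conduct of the trial, since contact by mail, then e-mail or telephone, is planned.

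Finally, the 1000 is marked as approximate and power is stated as a lower bound, so the 40-patient gap does not overturn the claim. The correction is editorial.

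The conflict over definition and rank is untouched by these objections, because it lies within the article itself. The ambiguity of the SD also remains.

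**Conclusion.** The point holds as a modest improvement plus two corrections on the page.

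- **Efficiency.** Adjusting for the collected baseline multiplies the change-score variance by (1 + r)/2: 0.75 at r = 0.5 and 0.85 at r = 0.7. If 2.5 is the SD of change, power at 960 goes from about 87% to about 95% or 92%. This rests on the assumed r and on equal variances at the two times.
- **Undefined SD.** If 2.5 is the raw-score SD and r is 0.3, the stated >80% would fail for an unadjusted change score (about 75%) and hold with adjustment (about 90%). The document does not establish that this is the case.
- **Arithmetic.** 80% of 1200 is 960. Power is about 87% instead of 88.5%, so >80% stands.
- **Outcome definition.** The four places that list or power quality of life as an outcome disagree on what it is or where it ranks, and must be reconciled.

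None of this bears on the primary outcome or on the size of the trial.

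**What to change.** 1. Name one baseline-adjusted analysis as the main quality-of-life comparison. This can be ANCOVA at each time point, or a linear mixed model with baseline score, arm, time, arm-by-time and centre that includes every patient with any follow-up.
2. State whether 2.5 is the SD of the change or of the raw score. If it is the raw-score SD, give the assumed correlation.
3. Replace the completion figure with 80% (960 patients, power about 87%), or keep 1000 and call it 83%.
4. Align the Abstract, Table 1, Outcomes and the power paragraph so that the between-arm difference in PROMIS score has one definition and one rank. Changing the Outcomes section alone would leave Table 1 in conflict. Keep the association with delirium among the pre-specified additional analyses, where item c already has it.

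The cost is wording only. Baseline, 30-day and 1-year scores are already collected, and neither the sample size nor the trial's procedures change. The one drawback is a slightly lower stated number of completers.

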### Strengths of the study and limitations

**
*Strengths.*
** Several important strengths can be ascribed to the ENGAGES-Canada study. The clinical trial is randomized, pragmatic, includes high volume sites, and is conducted in real life settings. The interventions to avoid EEG suppression are easily implemented and the primary outcome, the incidence of delirium, is of tremendous importance to patients, health care systems and society. In relation to the primary outcome (delirium incidence), the CAM instrument has been validated against reference standard DSM-IV and DSM-IV-TR criteria in multiple studies, and has been appraised as one of the two most reliable instruments for detecting delirium in a research context
^
57
^. The CAM long form has been demonstrated to have excellent psychometric properties for both hypoactive and hyperactive delirium
^
58
^. Programmatic training, coupled with the highly structured use of the CAM long form (as we are doing in the trial), has demonstrated excellent inter-rater reliability of researchers
^
28,
59
^. In addition, by complementing the CAM long form (or CAM-ICU) with validated chart review
^
49
^, we are bolstering delirium detection and minimizing missing primary outcome assessments. Since many components of the study are already incorporated into existing processes and infrastructures at participating Canadian sites, its implementation can be efficient. Enrollment is easily achieved within the flow of the clinic. The study is largely conducted by anesthesiologists and is integrated into the course of their clinical workday. Randomization is implemented in the operating room at the point of patient care because the anesthesia protocols do not require any advanced preparation or lead-in time. Enrollment of vulnerable patients 60 years old and older allows us to study a population that is understudied in clinical research. The importance of studying and understanding this targeted population lies in the potential of significant benefits from reducing the incidence of postoperative delirium and its related outcomes. Secondary outcomes such as patient-reported health-related quality of life factors are especially relevant to older patients who remain a largely understudied population. Trial feasibility is enhanced by the participation of investigators from multiple disciplines, who as a group has managed to establish a track record of successful collaboration and the completion of several major clinical trials (Canadian PACT group
^
60–
62
^). Since EEG guidance of anesthesia is straightforward and inexpensive, positive results from the study could provide strong effectiveness evidence, and would facilitate implementation, sustainability and dissemination of the EEG-guided protocol on a national level in Canada, as well as in other countries.

**
*Limitations.*
** Some limitations for the trial should be considered. The EEG-guided protocol can only be effective if anesthesiologists adhere to it. Including patients in a clinical trial aiming at the prevention of the incidence of postoperative delirium and providing patients and family members with educational material on the subject could possibly decrease the incidence of postoperative delirium. Three methods of assessment will be used to diagnose postoperative delirium, a pragmatic structured chart review, the full CAM and the CAM-ICU. The CAM-ICU has a decreased sensitivity compared to the CAM long form. However, the CAM-ICU is broadly used and has been validated for patients who are unable to speak (i.e., with a tracheostomy or a breathing tube in place). Available data from participating centers indicate that the vast majority of patients enrolled in the in the study will be extubated within the first 48 hours. As a result, delirium assessment will usually be obtained with the more specific and sensitive instrument – the CAM long form. Since the 30-day and the 1-year follow-ups for patient are based on self-report outcome measures, a potential limitation is an incomplete follow-up at these periods in time. Consequently, a sensitivity analysis was performed in our power calculations to take into account this possible attrition (80% response rate at 30-day and at 1-year). We plan to improve follow-up by contacting patients first by mail and, if unsuccessful, by e mail or telephone calls. Postoperative delirium could be missed with recurrent assessments because it is well known to be a fluctuating disorder. In our efforts to minimize missed diagnosis of postoperative delirium, we have included a structured chart review. This validated complementary approach has been shown to increase the detection of postoperative delirium
^
48,
49
^.

### Potential risks, alternatives and benefits

**
*Benefits.*
** If our hypotheses are confirmed, patients randomized into the group with the EEG-guided anesthesia will have a greater chance of avoiding postoperative delirium and its consequences’ downstream; including decrement in quality of life, falls, and cognitive decline. Evaluation of any potential unanticipated negative effects of EEG-guidance by investigating this range of psychiatric, cognitive, and functioning outcomes will also be possible.

**
*Risks.*
** There are few risks associated with this study. Breach of confidentiality is a rare risk. Psychiatric symptom self-report measures may also cause patients temporary distress, but it may also provide the opportunity for distressed patients to obtain community mental health resources and/or appropriate referral. EEG guidance of anesthesia poses a theoretical risk of intraoperative movement and/or awareness with recall. Nevertheless, previous studies have not found an increased incidence of awareness with randomization of patients to protocols using EEG guidance of anesthesia
^
14,
15,
63
^. In our study, intraoperative awareness with recall will be tracked within 48 hours of extubation postoperatively with a modified Brice interview
^
64
^ (see extended data
^
32
^). Review of adverse events by a data-safety monitoring committee and the PI, in consultation with the institutional review board, might lead to the recommendation to stop the trial in the event of increased reporting of intraoperative awareness in the EEG-guided group. In the informed consent for this study, patients are made aware of the rare risk of intraoperative awareness with recall. Serious side effects will be reported to the Ethics Committees and to the study’s data safety monitoring board. There is no financial compensation for the participating patients and all expenses related to the study are incurred by the participating research sites.

